### Provisions for post-trial care {30}

Post-trial care is not planned. Patients who suffer harm from trial participation will be cared for in the intensive care unit. Should prejudice linked to study participation occur, financial compensation will be provided by the insurance (Société Hospitalière d’Assurances Mutuelles—SHAM, [name], France; contract number: 143.380) contracted by the promotor (Hôpitaux Universitaires de Strasbourg).

At 6 months, the respiratory status will be assessed using the modified MRC dyspnoea questionnaire [47, 48] and a chest X-ray.

### Outcomes {12}

#### Primary endpoint

The primary endpoint will be the incidence of moderate-to-severe hypoxaemia (PaO_2_/FiO_2_ < 200, according to the Berlin definition [5]) in severe trauma patients (ISS > 15) during the first 7 ICU days. The PaO_2_/FiO_2_ ratio will be computed at least once daily (8:00 a.m.) together with the supine chest X-ray and the worst daily PaO_2_/FiO_2_ value will be taken into account to define hypoxaemia severity. In ARDS patients, the severity of hypoxaemia allows for its classification according to the Berlin definition and is strongly associated with mortality, length of recovery and quality of life [6, 7].

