### Who will take informed consent? {26a}

Inclusion will be feasible after patient approval, relative approval or emergency consent procedure (according to French law [42]).

Subsequent confirmation of consent will be obtained from the relatives and from the patient as soon as possible. The consent forms are available from the corresponding author on request.

After primary haemostasis and emergent surgical interventions, patients will be randomized in the ICU within 6 h. In the case of emergent surgical intervention before ICU admission, a maximum delay of 18 h will be tolerated from hospital admission (trauma bay) to study drug administration. Day 0 will be considered the day of ICU admission.

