#### Intervention description {11a}

Treatment with either dornase alfa or placebo will be administered using aerosol (Aerogen solo) in the ventilation circuit once per day (average treatment length: 7 min) for the first 2 days. The Aerogen device was shown to optimize dornase alfa deposition in the distal lung airways [43, 44]. Dornase alfa has an excellent safety profile and aerosolized NaCl 0.9% has a neutral effect on lung physiology.

The variables under study will be gathered every day and recorded on the electronic clinical research form (CleanWeb; Telemedicine Technologies S.A.S., Boulogne Billancourt, France).

For safety purposes, patient variables will be closely monitored before, during and within the first post-administration hour: lowest SpO_2_, maximal value and maximal increase in peak inspiratory airway pressure, maximal value and maximal increase in plateau airway pressure, extreme values of heart rate and mean arterial pressure, skin erythema, urticaria and variations in central temperature exceeding 1 °C.

During the first 7 days, at least one blood gas analysis and chest X-ray will be performed every day at 8:00 a.m. to compute the primary endpoint: presence or absence of ARDS and severity of hypoxaemia according to the Berlin definition. Additional blood gas analysis will be allowed and the worst daily PaO_2_/FiO_2_ ratio will be considered.

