### Participant timeline {13}

The total duration of participation in the study will be 30 days. The forecast study duration is 36 months from first to last patient recruitment (Table 1).

**Table 1 Tab1:** Template of recommended content for the schedule of enrolment, interventions and assessments

	Visit				
	Information	Enrolment	Allocation, visit 0	Post-allocation, visits 1–7	Close-out
Timepoint	Day 0	Day 0	Day 0	Days 1–7	Day 30
Location	Hospital	Hospital	Hospital	Hospital	Hospital
Next of kin information	X*	X*	X		
Signed informed consent		X*			
Plasma **β**HCG assay		X(*)			
Eligibility criteria check	X*	X*	X*		
Randomization			X*		
Study drug administration			X*^d^	X*^d^	
Clinical examination^a^		X	X	X	
Diagnostic tests^b^		X	X	X	
Blood assay^c^			X*	X*	
Adverse effect recording		X*	X*	X*	X*
Concomitant medications		X	X	X	X

*βHCG* beta human chorionic gonadotropin, *X* diagnostic test performed on a daily basis according to the standard of care in participating centres, *X** diagnostic tests performed for the purpose of the TRAUMADORNASE study

^a^Clinical examination includes physical examination (auscultation of the chest, central body temperature, positive end-expiratory pressure and inspired oxygen fraction levels) and recording of Utstein criteria [49]

^b^Diagnostic tests include arterial blood gases, chest X-ray, leukocyte and platelet counts, creatinine, blood urea nitrogen, bilirubin and quantitative lung bacteriologic samplings (bronchoalveolar lavage fluid or protected specimen brush) in the case of suspected lung infection

^c^Blood withdrawal: 6 ml of blood on day 0, day 3 and day 5

^d^Study treatment will be given on day 0 and day 1

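### The primary endpoint window does not exclude blood gases taken before randomisation, so hypoxaemia already present at entry can count as an incident event and dilute the treatment effect

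*Protocol article*

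**What the plan says.** **Window.** The Primary endpoint section counts moderate-to-severe hypoxaemia "in severe trauma patients (ISS > 15) during the first 7 ICU days". The consent section {26a} adds "Day 0 will be considered the day of ICU admission". The worst daily PaO2/FiO2 "value will be taken into account to define hypoxaemia severity". Intervention description {11a} allows additional gases and also uses the worst of the day. No section limits scoring to gases taken after randomisation or after the first dose.

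**Sequence.** After haemostasis and emergency surgery, "patients will be randomized in the ICU within 6 h". Table 1, note d, states "Study treatment will be given on day 0 and day 1". Where surgery precedes ICU admission, "a maximum delay of 18 h will be tolerated from hospital admission (trauma bay) to study drug administration".

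**Baseline data.** Table 1 places diagnostic tests at enrolment, at visit 0 and at visits 1–7, and its note b reads "Diagnostic tests include arterial blood gases, chest X-ray" among others.

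**Protection against early events.** Eligibility {10} requires ventilation and an ISS above 15 but sets no PaO2/FiO2 limit. Stratification is by centre and severe traumatic brain injury. The primary model in Statistical methods {20a} has treatment group and a subject effect. It is then extended with potential confounders that are not named and that pass through stochastic search variable selection (SSVS). Study limitations also mentions adjustment where groups differ.

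**The concern.** The objective is to reduce incidence. A patient whose ratio is below 200 between ICU admission and randomisation is an event under the written rule, whatever the study drug does. Such patients are foreseeable: all are ventilated at inclusion, and the pathophysiology section lists lung contusion and aspiration among the direct causes of hypoxaemia in trauma. If their share is not small, the endpoint measures prevalence plus incidence. The expected difference then shrinks below the planned 15 points, and an effective treatment is more likely to be missed. Study limitations already calls a 15-point reduction ambitious, so there is little to spare.

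**Working it through.** **1. Which days count.** The primary objective places dosing in the first two ICU days, and Table 1 note d gives those as day 0 and day 1. By that counting the first seven ICU days are days 0 to 6, and day 0 includes time before randomisation. Table 1, however, lists the post-allocation visits as days 1–7, which is also seven days and starts after the day of the first dose. The article supports both windows.

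**2. The plan's own figure.** Sample size {14} gives 0.45 vs 0.30, 200 evaluable per arm raised to 250, and a difference of more than 0.12 to be shown. It states no error rate, power or posterior threshold, so 200 cannot be reproduced from its inputs alone. At two-sided 5%, 0.45 vs 0.30 needs 163 per arm for 80% power and 217 for 90%.

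Power here uses the normal approximation:

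power = Φ[(d − 1.96·SE0)/SE1], with SE0 = √(2·p̄(1−p̄)/n) and SE1 = √([p_C(1−p_C) + p_T(1−p_T)]/n).

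For n = 200, 0.45 vs 0.30: SE0 = 0.0484, SE1 = 0.0478, (0.15 − 0.0949)/0.0478 = 1.152, power 87.5%. A simulated Bayesian rule (posterior probability of benefit above 0.975) gives about 88%, so the frequentist form is a fair stand-in.

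**3. Adding pre-dose events.** Let q be the share of all patients below 200 before the first dose. The documents give no value, so q is an assumption, shown from 0 to 30%.

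- Scenario A: the 45% already includes pre-dose events, and the planned risk ratio of 0.30/0.45 = 2/3 acts only on later ones. p_C = 0.45; p_T = q + (0.45 − q)·2/3.
- Scenario B: 45% to 30% holds in patients event-free at first dose, with pre-dose events on top. p_C = q + (1 − q)·0.45; p_T = q + (1 − q)·0.30.

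Example, A at q = 10%: p_T = 0.10 + 0.35·2/3 = 0.333; d = 0.117; SE0 = 0.0488; SE1 = 0.0485; (0.1167 − 0.0957)/0.0485 = 0.433; power 67%.

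| q | A: rates | A: difference (points) | A: power | B: rates | B: difference (points) | B: power |
|---|---|---|---|---|---|---|
| 0 | 45.0 vs 30.0% | 15.0 | 88% | 45.0 vs 30.0% | 15.0 | 88% |
| 5% | 45.0 vs 31.7% | 13.3 | 79% | 47.8 vs 33.5% | 14.3 | 83% |
| 10% | 45.0 vs 33.3% | 11.7 | 67% | 50.5 vs 37.0% | 13.5 | 78% |
| 20% | 45.0 vs 36.7% | 8.3 | 40% | 56.0 vs 44.0% | 12.0 | 67% |
| 30% | 45.0 vs 40.0% | 5.0 | 17% | 61.5 vs 51.0% | 10.5 | 56% |

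All at 200 per arm, two-sided 5%. If all 250 per arm were evaluable, power would be 76% (A) or 86% (B) at q = 10%, and 47% or 77% at q = 20%.

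**4. Effect needed to reach 30% under A.** The risk ratio on later events would have to be (0.30 − q)/(0.45 − q): 0.20/0.35 = 0.57 at q = 10% and 0.10/0.25 = 0.40 at q = 20%, instead of 0.67. At q = 30% every later event would have to be prevented.

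**5. Restricting to patients at risk.** Under A at q = 10%, 180 per arm remain, with risks 0.35/0.90 = 38.9% vs 25.9%. Power is 75%, against 67% for the endpoint as written.

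**The case against.** **Day 0 may not count.** A reader might infer that day 0 gases certainly enter the endpoint. The text does not say so. Table 1's days 1–7 give exactly seven post-allocation visits, and with a first dose on day 0 those gases would follow treatment. That reading is possible. It does not settle the matter, because the objective with note d points to day 0 as the first ICU day. Nor would it help a patient who is hypoxaemic at entry and still below 200 on day 1.

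**Adjustment is planned.** It would be wrong to say there is none. Only the covariate names are absent, and these may stand in the statistical analysis plan. The point therefore rests on the window and the open entry criterion, which the protocol fixes. Adjustment would in any case not remove pre-dose events from the outcome.

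**The 18 h limit.** It is tempting to read this as 18 h of pre-dose scoring. It runs from hospital admission and applies only when surgery comes before ICU admission. Time in the trauma bay and operating theatre lies outside an ICU-day window.

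**Bias.** Pre-dose events precede treatment and are balanced on average by randomisation. Neither arm is favoured, and the harm is lost power and a mislabelled quantity.

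**Magnitude.** The share q is unknown, and the planned 45% to 30% may already allow for early events. This is why both scenarios are shown. Enrolling patients whatever their oxygenation is a legitimate choice, but the endpoint then has to separate baseline status from new events.

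**Conclusion.** The point holds in limited form. The article does not exclude pre-randomisation gases from its primary endpoint, and its window can be read as days 0–6 or days 1–7. With no PaO2/FiO2 limit at entry and no named baseline oxygenation covariate or stratum, hypoxaemia present at entry can be counted as incident. The expected difference falls from 15 points to 11.7–13.5 at q = 10% and to 8.3–12 at q = 20%. Power falls from about 88% to 67–78% and 40–67%.

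These figures assume 200 evaluable per arm, a two-sided 5% test standing in for an unstated Bayesian criterion, pre-dose events that treatment cannot alter, and a q that the documents do not supply. They give a range of possible loss, not an estimate for this trial. The documents do not support a claim of bias towards one arm, of certain inclusion of day 0 values, or of no covariate adjustment.

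**What to change.** 1. In the Primary endpoint section, state the first and last day of the window and count only PaO2/FiO2 values from gases taken after randomisation. Anchoring on randomisation, not on first dose, gives every randomised patient a window, dosed or not, in line with the intention-to-treat analysis in {20b}. Align Table 1 with the chosen days.
2. Name the last pre-randomisation PaO2/FiO2 as a continuous covariate that is forced into the primary model and not subject to SSVS selection. Table 1 already places blood gases at enrolment.
3. Pre-specify a supporting analysis in patients with a baseline ratio of 200 or above, which estimates true incidence.
4. Separately, reconcile the endpoint wording. Sections {11a} and {11c} describe the primary endpoint as "presence or absence of ARDS and severity of hypoxaemia according to the Berlin definition", whereas the Primary endpoint section and the model use hypoxaemia below 200, yes or no. Use the latter throughout and report ARDS on its own.

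**Cost.** Protocol and analysis-plan wording, and a recorded time for each scored gas. Recruitment began in March 2019, so times for patients already enrolled may have to be retrieved, and the change should be fixed while the data are still blinded. The supporting analysis has fewer patients. Those with persistent baseline hypoxaemia still count as events in the primary analysis, so the change recovers only part of the loss.

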#### Secondary objectives

The secondary objectives are to demonstrate, using aerosolized dornase alfa as compared to placebo, an improvement in static lung compliance, a reduction in mechanical ventilation duration or an increase in ventilation-free ICU days, a reduction in the length of ICU stay, a reduction in the hospital length of stay, a reduction in the incidence of multi-organ failure, a reduction in the incidence of ventilator-associated pneumonia (VAP) and a reduction in mortality at day 30.

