The aim of this study is to show that the frequency of moderate-to-severe hypoxaemia is lower in the dornase alpha group than in the placebo group. The main variable is then dichotomous “moderate-to-severe hypoxaemia yes/no”, modelled in a logistic mixed regression. We will assume that this variable is Bernoulli distributed with parameter π. The logit of this parameter (linear predictor) is additively written as:
$$ \mathrm{logit}\left({\pi}_i\right)={\alpha}_0+{\alpha}_1I\left({g}_i=1\right)+{\beta}_i, $$

where:
*α*_0_ is a grand mean, with mean 0 normal prior (the variance in this normal is 6, corresponding to a low informative prior)*I*(*g*_*i*_ = 1) is a dummy covariate coded for the group of subject *i* (1 for the dornase alpha group and 0 for the placebo group) — the prior on the parameter of this covariate is the same normal as that for the grand mean*β*_*i*_ is a (random) subject effect, on which is assumed a normal prior with mean 0 and low variance (e.g. 10)

Because the linear predictor is on the logit scale, the probability for moderate-to-severe hypoxaemia will be obtained by monitoring the back-transformation of the logit.

This regression model without covariates except group will be completed for taking into account potential confounding variables. In the model, the entire set of these variables will be added and, secondly, selected using stochastic search variable selection (SSVS) [53]. In such a model, the prior distribution on each parameter is a mixture of two mean 0 normal distributions, one with low variance and the other with high variance: if the posterior weight on this second normal is strongly around 0, then the prior on the parameter is essentially driven by a normal distribution whose mean is centred on 0; this is the clue for a “non-significant” parameter.

The secondary analyses will be conducted as the main analysis with a regressive model, testing the difference of a parameter between the two groups. Only the likelihood model will be changed to take into account the type of variable studied: γ distribution for continuous variables such as length of stay and duration of ventilation. Dichotomous variables such as 30-day mortality will be studied with logistic regression.

No statistical procedure for replacing missing values will be used. All variables and subjects will be considered in the descriptive analyses, but, for inference, 20% missing data or more will result in rejection of the variable or individual.

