#### Methods in analysis to handle protocol non-adherence and any statistical methods to handle missing data {20c}

No statistical procedure for replacing missing values will be used. All variables and subjects will be considered in the descriptive analyses, but, for inference, 20% missing data or more will result in rejection of the variable or individual.

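### The primary endpoint gives death in the 7-day window no role, so under either reading of the protocol article an excess of early deaths on dornase alfa could make the primary result look better than it is

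*Protocol article*

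**What the plan says.** Under Outcomes {12}, Primary endpoint, the protocol article states: "The primary endpoint will be the incidence of moderate-to-severe hypoxaemia", with a PaO2/FiO2 ratio below 200 as the threshold, "in severe trauma patients (ISS > 15) during the first 7 ICU days". At least one gas is taken each day, and "the worst daily PaO_2_/FiO_2_ value will be taken into account to define hypoxaemia severity".

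Statistical methods {20a} turns this into one binary variable per patient: "The main variable is then dichotomous “moderate-to-severe hypoxaemia yes/no”, modelled in a logistic mixed regression". The model has a group term and a subject effect, and no time-to-event or competing-event element. Section {20b} makes intention to treat the main analysis, with a per-protocol analysis added.

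On missing data, {20a} and {20c} say the same: "No statistical procedure for replacing missing values will be used", and "for inference, 20% missing data or more will result in rejection of the variable or individual".

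Death appears only as a separate outcome. The Secondary objectives name "a reduction in mortality at day 30", and the Secondary endpoints list mortality at that time. Nothing says how a patient is classified who dies within the first 7 ICU days without a ratio below 200.

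**The concern.** Death ends the blood gases and so competes with the primary event. A patient who dies on day 4 with a worst ratio of 230 can no longer become a *yes*. A survivor whose ratio falls to 190 on day 5 is a *yes*. If the first patient is a *no*, the death is scored as the better result. If that patient is rejected, the death disappears from the comparison.

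Deaths in the window are foreseeable. Eligibility {10} requires an ISS above 15 and mechanical ventilation. It removes patients with a life expectancy under 24 h or a do-not-resuscitate order, which reduces deaths on the following days but does not prevent them. The Background attributes secondary ICU deaths after trauma to multi-organ failure and ARDS, so death may be linked to the process the endpoint measures.

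What is at stake is direction. If the drug raised early mortality, the primary contrast could move in its favour.

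**Working it through.** **Inputs from the article.** Placebo incidence 0.45 (Sample size {14}); window of 7 ICU days; binary outcome; rejection at 20% or more missing. The article gives no figure for deaths in the window, so there is no plan figure to reproduce.

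**Step 1: what the 20% rule does to an early death.** The rule does not say whether it counts daily gases or all of a patient's variables, or whether days after death are missing. If it counts daily gases and they are:

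- 7 days: one lost day is 1/7 = 14.3% (kept); two are 2/7 = 28.6% (rejected).
- 8 days (days 0 to 7): one lost day is 1/8 = 12.5% (kept); two are 2/8 = 25% (rejected).

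On that reading only a death that costs a single day stays in, as a *no*. If days after death are not missing data, all such patients stay in as *no*.

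**Step 2: effect on the contrast.** Let p be the hypoxaemia risk had nobody died early, d the share who die in the window before a qualifying gas, and q the share of those who would have become hypoxaemic.

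- Deaths coded *no*: p − qd
- Deaths excluded: (p − qd)/(1 − d)
- Hypoxaemia or death: p − qd + d

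Assumptions, none from the article: no effect on hypoxaemia (p = 0.45 in both arms); d = 0.10 on placebo and 0.15 on dornase alfa. Each cell shows placebo v dornase alfa; the sign in brackets is placebo minus dornase alfa, so plus looks like benefit.

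| Who dies early | Coded *no* | Excluded | Hypoxaemia or death |
|---|---|---|---|
| Unrelated to risk (q = 0.45) | 40.5% v 38.25% (+2.25) | 45% v 45% (0) | 50.5% v 53.25% (−2.75) |
| All would have been hypoxaemic (q = 1) | 35% v 30% (+5.0) | 38.9% v 35.3% (+3.6) | 45% v 45% (0) |
| None would have been (q = 0) | 45% v 45% (0) | 50% v 52.9% (−2.9) | 55% v 60% (−5.0) |

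For example, in row 1, coded *no*: 0.45 − 0.45 × 0.10 = 0.405 and 0.45 − 0.45 × 0.15 = 0.3825. In row 2, excluded: 0.35/0.90 = 0.389 and 0.30/0.85 = 0.353.

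Coding as *no* pushes towards benefit unless none of those who die would have become hypoxaemic. Exclusion pushes towards benefit only when q exceeds p. The composite never shows a false benefit here, but at q = 1 it shows no difference at all despite the excess deaths, so deaths by arm are needed beside it.

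**Step 3: no excess, no false benefit.** With equal d, equal q and equal p, every column gives a difference of 0.

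**Step 4: chance of a misleading result.** A two-sided 0.05 z-test at 250 per arm, as a stand-in for the Bayesian model, has a 2.5% chance of favouring dornase alfa under the null. With early deaths of 5% v 10%, this becomes 7.4% (q = 0.45) to 21% (q = 1) if deaths are coded *no*, and 2.5% to 10.4% if they are excluded and the analysed numbers shrink accordingly.

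**The case against.** The strongest reply is that the article never says such patients are coded *no*. A reader might infer that the plan scores the dead as successes. The documents do not support that as a statement of fact: the 20% rule may remove those patients, and if death is unrelated to hypoxaemia risk, removal leaves no bias. This stands, and it is why the point covers both readings.

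Next, a condensed article may leave the classification of deaths to a full protocol or SAP that is not shown. That is fair for a derivation detail. But the article itself fixes the endpoint, the model, the analysis population and the rejection rule, and together these leave an early death before a qualifying gas with no unfavourable weight.

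The size may also be small. Patients dying of ARDS will often already have a qualifying gas, since the worst daily value counts. Required ventilation beyond 48 h and the do-not-resuscitate exclusion limit early deaths. If death is unrelated to risk and coded *no*, a false 15-point benefit needs 0.15/0.45 = 33 points of excess early mortality. All of this stands.

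Finally, harm would not be hidden: day-30 mortality is a secondary endpoint, the DSMB meets after 20 patients and then after every further 100, and the interim analysis allows stopping for harm. These limit the damage but do not correct the primary contrast.

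**Conclusion.** The point holds as a weakness of the primary analysis that should be repaired. Death in the window has no role, and the two available readings (*no*, or rejection) can both favour the arm with more early deaths. Rejection also conflicts with intention to treat.

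In the example of 10% v 15% early deaths and no effect on hypoxaemia, the false benefit is 2.25 points when deaths are coded *no* and unrelated to risk, and 5 points at the extreme. Under exclusion it is 0 and 3.6 points for the same two cases, and it reverses if those who die were at lower risk. These sizes rest on assumed death rates and on an excess on dornase alfa, neither of which the article gives.

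A reader might also infer that equal early deaths dilute the 45% v 30% contrast and leave the trial undersized. The article does not support this. It gives 45% simply as an incidence, and if early deaths are already in that denominator, multiplying by (1 − d) counts them twice. Even on that calculation, equal deaths of 5, 10 or 15% leave 0.15 × (1 − d) = 14.25, 13.5 or 12.75 points, all above the 0.12 difference in Sample size {14}.

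**What to change.** Keep a PaO2/FiO2 ratio below 200 as the primary event, and add:

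1. Patients who die within the first 7 ICU days stay in the primary analysis, classified by the gases taken while alive. Days after death are not counted as missing under the 20% rule.
2. A pre-specified supplementary analysis of moderate-to-severe hypoxaemia or death within the 7-day window, in all randomised patients, with the same Bayesian logistic model.
3. Deaths in the window, by arm, reported beside the primary result.

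Item 1 settles the classification and respects intention to treat, but it keeps the *no* coding in the primary analysis, so items 2 and 3 are needed to show whether early deaths explain an apparent benefit. The benefit claim should not be made formally conditional on item 2: that would add a success criterion whose operating characteristics have not been worked out.

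The cost is a few sentences, one further model run and one table row. The timing of death within the window is needed. The article does not say that date of death is recorded, but daily visits to day 7 and follow-up to day 30 should supply it. The downside is that deaths unrelated to the lung add noise to the composite.
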